Several studies exploring mental health impact of the current COVID-19 pandemic and risk factors for this have since been performed (Kisely et al., 2020). Whilst some individual studies have suggested an increased anxiety and risk of mental health problems in HCPs compared to non-HCPs (Zhang et al., 2020), subsequent meta-analyses have found a similar prevalence of anxiety and depression between healthcare workers and healthy controls from the general public (Krishnamoorthy et al., 2020; Luo et al., 2020; Pappa et al., 2020).

This observation can, in part, be explained by the different roles of HCPs. A study by Lu et al. (2020) demonstrated higher levels of psychological distress in HCPs working in hospital, compared to administrative staff. Work-related risk factors including close contact with infected patients, level of work experience and organizational support provided have also been shown to impact the psychological effect of emerging virus outbreaks (Kisely et al., 2020). These effects may be more prominent in junior or trainee doctors likely due to having to work in unfamiliar environment, with disrupted training and variable supervision (Kisely et al., 2020).

Healthcare professionals work under different schedules, including regular office hours, shift work, and swing shifts. Shift work and stressful work-related situations have been linked to poor mental health (Torquati et al., 2019). There is an established body of literature that has demonstrated the prevalence among physicians of a range of sleep-related issues, substance use and mental health disorders (Mihailescu and Neiterman, 2019; Petrie et al., 2019). These problems increase the risk of burnout or errors on the job. In those with pre-existing mental health disorders, there may be increased psychosocial problems, an increased risk of suicidal behavior, increased alcohol, or other psychoactive substance use, or a more severe form of the viral illness (Possamai, 2007; Greenberg et al., 2020).

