## Study Questionnaire and Dissemination

This will be achieved through a wide distribution of the electronic survey to HCPs and non-HCP controls. We will seek endorsement and support from professional societies and associations in the United Kingdom and other parts of the world to disseminate this widely. Distribution networks that will be considered include network email distribution lists and relevant social media platforms.

We expect to have a larger distribution of the questionnaire in the United Kingdom, but we are aiming at achieving an international cohort of participants. Within the United Kingdom, dissemination will be through different NHS Trusts, geographically distinct deaneries involving with overseeing medical training, scientific and medical societies and universities. On an international level we will involve international medical and allied health scientific societies and associations.

There will be an invitation to join the study including an explanation of the reasons of the survey. Any participant taking part in the survey based on the brief description of the study will be deemed to have consented for the study, and no other consent will be required. This cross-sectional survey will include basic information about the participant including demographics, living circumstances, education level and pre-existing physical and mental health conditions. It will also include questions regarding work experience and profession, work circumstances and exposure to COVID-19. Table 1 provides a summary of the aspects assessed and the tools used.

**TABLE 1 T1:** Study variables and respective assessment tools.

Variables	Assessment Tool

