### Method of Analysis

We will use the STATA 15 statistical software for analysis. Chi-square test will be used to compare the difference in prevalence of anxiety, depression and other variables between the groups at baseline. We will evaluate for changes in proportion of those outcomes at baseline to the end of the study using paired McNemar test. We will use logistic regression to assess the factors at baseline related to development of physical symptoms, overall, and in the HCPs group alone. Data will be described using appropriate descriptive statistics.

We will collect information for potential confounding factors such as age, gender, education level, and health conditions from both HCPs and their controls and adjust for these in the analysis. For all validated tools, we will use appropriate and previously published cut-offs to categorize them. For example, for the primary end point of anxiety, we will use the cut-off related to moderate anxiety, but also do a sensitivity analysis using cut-off using “mild” anxiety definition. Similar and consistent strategy will be followed for other validated tools. We will perform logistic regression for binary outcomes, such as those listed in our primary and secondary outcomes, after adjusting for pre-defined confounders including age, gender, and years of education. The choice of these *a priori* confounder is based on the significant association that exists for most of the study outcomes. We have also adjusted for time since the self-identified peak of the pandemic as this will impact on outcomes such as anxiety and depression. However, for the outcome of developing COVID-19 infection and change in prevalence of COVID-19 infection, we will also adjust for pre-existing medical conditions.

We will also stratify HCPs according to their roles (doctors, nurses, pharmacists, healthcare assistants etc.), and will evaluate and compare the endpoints by respective roles. Comparison between HCPs from the United Kingdom and outside will be undertaken adjusting for the self-identified peak of the pandemic in that region. We also will assess whether the years of experience (as a categorical variable) has any impact on the measured outcomes.

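### The UK versus non-UK comparison of healthcare professionals names no adjustment for role or years of experience, so a difference in professional mix may be read in part as a country effect

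*Protocol article*

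**What the plan says.** Secondary objective 5 compares UK healthcare professionals (HCPs) with HCPs in five other world regions. Method of Analysis gives this comparison its own sentence: "Comparison between HCPs from the United Kingdom and outside will be undertaken adjusting for the self-identified peak of the pandemic in that region".

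The same section sets a general rule for binary outcomes: logistic regression "after adjusting for pre-defined confounders including age, gender, and years of education". On timing it adds: "We have also adjusted for time since the self-identified peak of the pandemic". Pre-existing medical conditions enter only for the COVID-19 infection outcomes.

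Role and experience appear elsewhere in the section, but as comparisons in their own right. On role: "We will also stratify HCPs according to their roles (doctors, nurses, pharmacists, healthcare assistants etc". On experience: "We also will assess whether the years of experience (as a categorical variable) has any impact on the measured outcomes". Contact with COVID-19 patients separates Groups 1 and 2 and is not named as a covariate.

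The Introduction treats these variables as influences on psychological outcomes in outbreaks: "Work-related risk factors including close contact with infected patients, level of work experience and organizational support provided have also been shown to impact". It also attributes inconsistent earlier findings partly to differing HCP roles, and suggests stronger effects in junior or trainee doctors.

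Study Questionnaire and Dissemination describes the channels. For the UK: "Within the United Kingdom, dissemination will be through different NHS Trusts, geographically distinct deaneries involving with overseeing medical training". That sentence then goes on to scientific and medical societies and universities. For other countries: "On an international level we will involve international medical and allied health scientific societies and associations". The same section says that profession, work experience and COVID-19 exposure are recorded.

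**The concern.** A variable confounds a country comparison if it affects the outcome and is distributed differently between the countries' samples. The article supports the first condition for role and experience in its own Introduction. It makes the second plausible, because employer and training-body routes are named for the UK only. The comparison in which recruitment is most likely to unbalance professional mix therefore names no adjustment for that mix.

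At stake is the reading of secondary objective 5. A difference in anxiety or depression prevalence between UK and overseas respondents could partly reflect who was reached, not where they work. The primary objectives are not affected.

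**Working it through.** **The plan's own figure first.** The article states no power or effect size for the UK comparison. Its baseline calculation (40% versus 30%, 800 versus 250, two-sided 0.05) reproduces: 82.2% by the pooled two-proportion z-test and 80.1% with continuity correction, against a stated figure of just over 80%. The 10-point gap is thus a sound input taken from the plan.

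**Inputs from the article**
- Prevalence: 40% in patient-facing HCPs and 30% in non-patient-facing HCPs (Sample Size).
- HCPs in total: 800 in Group 1 plus 125 in Group 2 = 925 (Participant Selection, Sample Size).

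**Assumptions, because the article gives none**
- No true country effect.
- UK share of HCPs from 50% to 80%.
- Patient-facing share of 90% in one sample and 80%, 70% or 50% in the other.

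Contact is used only because it is the one work-related factor for which the plan gives a prevalence gap. It shows how an imbalance turns into an apparent difference. The article has no corresponding figure for role or experience.

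**Formulas**
- Spurious difference = (difference in patient-facing share) × (0.40 − 0.30).
- Rejection probability = Φ[(d − 1.96·SE0)/SE1] + Φ[(−d − 1.96·SE0)/SE1], where d is the spurious difference, SE0 the pooled and SE1 the unpooled standard error.

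**One case in full: 90% versus 70%, split 50/50**
- First sample: 0.40 × 0.90 + 0.30 × 0.10 = 0.39. Second: 0.40 × 0.70 + 0.30 × 0.30 = 0.37. So d = 0.02.
- Odds ratio: (0.39/0.61)/(0.37/0.63) = 1.09.
- With 462.5 per sample, SE0 = √(0.38 × 0.62 × 2/462.5) = 0.0319, and SE1 is also 0.0319.
- (0.02 − 0.0626)/0.0319 = −1.33, lower tail 0.091. (−0.02 − 0.0626)/0.0319 = −2.59, lower tail 0.005. Sum: 9.6%.

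**All cases**

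| Patient-facing share | Spurious difference | Odds ratio | False-positive rate, 80/20 to 50/50 split |
|---|---|---|---|
| 90% vs 80% | 1 point | 1.04 | 5.6% to 6.1% |
| 90% vs 70% | 2 points | 1.09 | 7.8% to 9.6% |
| 90% vs 50% | 4 points | 1.19 | 16.7% to 24.2% |

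**Are these imbalances feasible?** Group 2 is 125/925 = 13.5% of planned HCPs. With the 90% sample being the UK, the 20-point case at 80/20 implies 0.8 × 10% + 0.2 × 30% = 14% non-patient-facing, which fits. At 50/50 it implies 20%. The 40-point case implies 18% at 80/20 and 30% at 50/50, which does not fit the planned numbers. The first two rows are the realistic range for contact alone, and the third is a stress case.

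**Limits.** These are crude contrasts, whereas the plan adjusts for age, gender, education and timing. Imbalance in role or experience could add to the bias or offset it, and the direction is not known.

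**The case against.** Four points on the other side carry weight.

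- **The covariate list is open.** It is introduced as including certain variables, the article is condensed, and a fuller plan could add role and experience. Age, in the general set, partly stands in for experience. This stands as a caution. However, the article does not defer this model: it states which adjustment the comparison receives, and age does not stand in for role.
- **The channels overlap.** A reader might infer that UK HCPs come through employers and training bodies and overseas HCPs only through societies. The article does not support that split. Societies are used in the UK too, endorsement is sought from societies in both settings, and email lists and social media are not tied to a region. What remains is that the UK has extra channels, which may change the mix.
- **Contact may be part of how country or role acts.** Adjusting for it could remove some of the difference that the objective asks about. This stands, so contact should not be a mandatory covariate. A reader might also infer that the role comparison under secondary objective 4 must be adjusted for contact. That is a choice of estimand, and leaving contact out is not an error.
- **The problem is partly acknowledged.** Study Limitations mentions selection bias, unknown confounders in an international study, and differences in pandemic phase and policy. Its remedy is basic demographics, and it does not mention professional mix.

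**Conclusion.** The concern holds as a moderate point on one secondary objective. The stated adjustment for the UK versus non-UK comparison leaves out role and years of experience, although the article itself links both to distress and already collects them.

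The size cannot be fixed from the article. With the plan's 10-point gap, 925 HCPs and an assumed imbalance of 10 to 20 points in patient-facing share, the spurious difference is 1 to 2 points and the false-positive rate about 6% to 10%. If the two samples have a similar mix, the bias is negligible.

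A reader might infer a bias of 5 points or more and a false-positive rate of a quarter or higher. The documents do not support that. It would need a prevalence gap for role or seniority that the article does not give, and imbalances all running in the same direction. Nor can an imbalance in contact arise within the 800 HCPs, since all of them are Group 1 by definition. Misreading mix as a country effect is a risk, not a certainty.

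**What to change.** In Method of Analysis, amend the sentence on the UK comparison so that the logistic model includes role and years of experience, along with the pandemic-peak term and the general covariates. Then:

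- tabulate role, years of experience and contact group (Group 1 or 2) by region, so that readers can see the achieved mix;
- as a sensitivity analysis, report the comparison with contact group added, or restricted to Group 1, beside the estimate without it, and say that contact may be part of how country acts;
- describe the result as an adjusted difference between volunteer samples.

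The role comparison needs no change on this account. The cost is a sentence or two of text, a few more model terms and slightly wider intervals. No new data are needed, because the baseline questionnaire already covers profession, work experience and COVID-19 exposure.

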## Ethical Considerations

### Ethical Approval

NHS Research Ethics Committee (REC) approval has been obtained for the study (protocol, consent form, all written material to be provided to the participant and all advertisements that may be used for participant recruitment). Appropriate reports on the progress and any other notifications of this trial by the Investigator will be made to the REC and the Sponsor in accordance with the applicable governance regulations and in agreement with policy established by the Sponsor.

### Risks, Burdens, and Benefits

There are no significant risks or benefits associated with participating in this survey.

There is an ethical concern about what we should do for participants in the cohort survey displaying mental or physical wellbeing concerns. We therefore clarify that our questionnaire remains a screening tool and does not provide final clinical diagnosis of any physical or psychiatric conditions. We emphasize the importance for participants to seek clinical advice from their occupational health department or GP, should they feel the need to. In addition, signposting or links to mental health support websites or services are provided on the survey platform and on our study website. These include (but not exclusive to): occupational health departments at workplace (general practitioner, Health Education England Professional Support Unit, FRONTLINE NHS helpline, MIND, health professional unions etc.).

### Informed Consent

Participant information sheet and consent will be available electronically on the study website. All participants are required to provide informed consent prior to completing the questionnaire.

## Study Limitations

This study has certain limitations. The online survey-based methodology relies on self-reported responses can be subjective. For example, survey responses may provide a one-sided interpretation of events and is dependent on participants’ recall. Non-response to optional questions may also limit data interpretation. There is the potential for selection bias which is inherent in studies with voluntary participation.

Whilst the survey questions attempt to address predicted confounders such as participant demographics, education level and physical and mental health, we acknowledge that there may be unknown confounders, particularly in a study conducted internationally. Although we try to control for this, we acknowledge that by including participants from multiple countries, we will capture responses occurring at different phases of the COVID-19 pandemic. There may also be heterogeneity in responses as a result of different financial and health policies adopted worldwide. We hope to account for some of these differences by collecting basic information regarding the participant’s demographics and characterizing these differences in our analysis.

Many of the limitations are inherent to the online questionnaire-based methodology, but we have chosen to balance the limitations against the benefits, which include easy accessibility and its ability to overcome geographical barriers.

## Discussion

As suggested by recent studies in this area, we expect that the COVID-19 pandemic will have a significant impact on the HCPs working on the frontline, and that this will have significant impact on their physical and mental health over the period of follow-up. Direct patient facing roles are expected to have negative impact on psychological and physical wellbeing, compared to non-patient facing roles or compared to the general public. In particular we expect that frontline HCP workers will have increased levels of anxiety, depression and sleep disorders compared to non-patient facing HCPs and control populations. We also hypothesize that, compared to controls, they will report significant behavioral changes regarding habits such as smoking, diet, and exercise, and that the pandemic will be likely to impact on their personal relationships. We also hypothesize significant changes in levels of burnout.

We surmise the adequate provision of appropriate PPE alongside necessary training will impact levels of anxiety as well as recorded absence from work. This stressful event may also have implications for the early and medium-term mental health of these workers and may also have an impact on their physical wellbeing.

### Relevance of Finding for Clinical Practice/Prevention

The findings of this study will help to outline the impact of the COVID-19 pandemic on HCPs, identify the needs of HCPs and help to improve design and delivery of support systems. The wellbeing of HCPs is vital in order for them to be able to continue providing the vital services during the pandemic and beyond. We plan to share the findings with healthcare leaders, the scientific community and individual staff members to allow better understanding and support structures for maintaining wellbeing.

## Ethics Statement

The studies involving human participants were reviewed and approved by the Cambridge East, Research Ethics Committee (20/EE/0166). The participants will provide their written informed consent to participate in the study via completion of the survey.
